#### Secondary outcome measures:

➢ Use of the system NHGDoc

Number of requests sent and alerts received for all patients; number of requests sent and alerts received for heart failure patients; percentage of opened alerts compared to the number received alerts; percentage of opened alerts compared to the number received alerts for heart failure patients; mean delivery time for an alert; number of practices that switched any module off; for each module, the number/percentage of practices with at least one user who switched the module off; and number of practices with at least one user who switched the module heart failure off (intervention group only).➢ Patient data registration

Percentage of consultations in which for a patient with heart failure, relevant patient data have been registered: clearance of creatinine (<12 mnd); (serum) creatinine (<12 mnd); (serum) potassium (<12 mnd); (serum) sodium (<12 mnd); patient weight (<6 mnd); heart (frequency) (<6 mnd); blood pressure (systolic and diastolic) (<6 mnd).➢ Hospital admissions

Number of hospital admissions of patients with heart failure.➢ All cause mortality

Number of patients with heart failure that died in the hospital.

### Sample size

The minimum required number of general practices was based on the two main primary outcome measures: prescribing of ACE-inhibitors/angiotensin II and prescribing of beta-blockers. The anticipated improvement was based on literature [27,28] as well as on consultation of experts in the field (ACE-inhibitor change from 63%–69%; beta-blockers from 59%–65%). As for beta-blockers, to detect this difference, we will need at least 122 general practices completing the trial with 80% power at a type I error risk (*α*) of 5%, taking an estimated intra-cluster correlation of 0.1 into account [34]. With this number of practices, the study will also be able to detect the difference for prescribing of ACE-inhibitors (minimum number of practices =116). We do not, however, expect to be able to detect an effect on hospital admissions and hospital mortality with this number of practices.

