**Methods:**

A cluster RCT will be conducted among 120 general practices in the Netherlands. Eligible general practices will be randomized to receive either the regular NHGDoc decision support modules (control arm) or the regular modules plus an additional module on heart failure (intervention arm). The heart failure module consists of patient-specific alerts concerning the treatment of patients with heart failure. The effect evaluation will focus on performance indicators (e.g., prescription behavior) as well as on patient outcomes (e.g., hospital admissions) relevant in the domain of heart failure. Additionally, a process evaluation will be conducted to gain insight into the barriers and facilitators that affect the uptake and impact of NHGDoc.

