### Randomization

Eligible general practices will be randomly allocated to either the intervention arm or the control arm, stratified by type of EHRS (MicroHIS X or Promedico-ASP) (see Figure 1). Practices will be the unit of randomization. Before randomization, the practices will be clustered at the level of practice addresses (practice AGB code and zip code) to avoid GPs and practices that are located within the same building being designated to different study groups. Randomization will be central and computer-generated, executed by an independent person (one of the members of the research team without any COI towards allocation). Dedicated software will be used to generate a randomization scheme with an equal number of control and intervention practices.

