### Analysis

To assess the effects of NHGDoc in terms of improving the quality of primary care, the scores on outcomes measures during the follow-up period will be compared between both study arms adjusted for baseline findings. To take into account potential clustering of effects within practices, multilevel models will be used.

The primary outcome measures are the percentage of consultations in which a patient with heart failure is prescribed 1. ACE-inhibitors/angiotensin II, 2. beta-blockers, and 3. diuretics. To assess the effects of NHGDoc on each of these variables, multilevel linear regression analysis will be performed. To assess the effects of NHGDoc on mortality, logistic regression analysis will be used, adjusting for severity of illness at hospital admission and comorbidity as measured by the Charlson Comorbidity Index. Both patient-level and practice-level intercept estimates will be used to account for potential correlation of measurements within patients and within general practices. We do not use the provider level estimates in our analyses as the difference between number of practices and providers will be too small due to solo practices. Moreover, patients may visit different GPs within the same practice during the year making this distinction less relevant as well.

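### On the printed inputs, 122 and 116 practices cannot be trial totals with 80% power; without credit for baseline adjustment, 120 practices give at most about 57% and 59%.

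*Protocol article*

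**What the plan says.** The Sample size section bases the number of practices on two of the three primary outcomes. The anticipated improvements are "ACE-inhibitor change from 63%–69%; beta-blockers from 59%–65" (per cent). For beta-blockers it concludes that "we will need at least 122 general practices completing the trial with 80% power at a type I error risk" of 5%, "taking an estimated intra-cluster correlation of 0.1 into account". For ACE-inhibitors it gives "minimum number of practices =116". It does not use the words per arm, gives no cluster size and claims no gain from baseline adjustment.

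Three other places fix how the figures are used. The abstract states that "A cluster RCT will be conducted among 120 general practices in the Netherlands". The Randomization section plans a "randomization scheme with an equal number of control and intervention practices". The Analysis section says that "the scores on outcomes measures during the follow-up period will be compared between both study arms adjusted for baseline findings".

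**The concern.** Taken together, these places make 122 the size of the whole trial, about 61 practices per arm. With an ICC of 0.1, adding patients within a practice soon stops helping, so the number of practices per arm has a floor that no cluster size can undercut. If that floor lies above 61, the printed inputs do not deliver the printed power. The power claim is the stated basis for the trial's size. It also shapes how a non-significant result on the two main outcomes would be weighed: such a result is weaker evidence against a 6-point effect if the power was well below 80%.

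**Working it through.** **Inputs.** From the Sample size section: 59% vs 65% (beta-blockers), 63% vs 69% (ACE-inhibitors), alpha 5%, power 80%, ICC 0.1. From the Randomization section: equal arms. From the abstract: 120 practices. Two assumptions: a two-sided test (sidedness is not stated) and m observations per practice (not stated, so varied).

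**Individual sample size per arm.** n = (1.96 + 0.8416)² × [p1(1−p1) + p2(1−p2)] / 0.06²
- Beta-blockers: 7.849 × (0.2419 + 0.2275) / 0.0036 = 1,023.4
- ACE-inhibitors: 7.849 × (0.2331 + 0.2139) / 0.0036 = 974.6

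**Practices per arm.** k = n × [1 + (m−1) × 0.1] / m = n × (0.1 + 0.9/m). As m grows, k falls towards 0.1n and never below it:
- Beta-blockers: 102.3, so at least 103 per arm (206 in total)
- ACE-inhibitors: 97.5, so at least 98 per arm (196 in total)

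**Trying to reproduce 122 and 116.**
- As totals (61 and 58 per arm): both lie below the floor, so no m solves the equation. The pooled-variance, continuity-corrected and arcsine formulas give floors of 102.6, 105.9 and 102.6 for beta-blockers, and the same conclusion. One-sided testing lowers the floors to 80.6 and 76.8, still above 61 and 58.
- As per-arm numbers: 122 solves at m = 46.9 and 116 at m = 47.3. With rounding up, m = 48 gives 121.5 and 115.7, hence 122 and 116. With the pooled formula, m = 50 gives 121.1 and 115.3, hence the same pair. The totals would then be 244 and 232.
- As totals with credit for baseline adjustment: let r be the correlation between a practice's baseline-year and follow-up-year percentage, and multiply the variance by (1−r²). The total is 2n × (0.1 + 0.9/m) × (1−r²). At r = 0.75 and m = 25 this is 2 × 1,023.4 × 0.136 × 0.4375 = 121.8, and 2 × 974.6 × 0.136 × 0.4375 = 116.0, hence 122 and 116. The pairs r = 0.70 with m = 54 and r = 0.80 with m = 14 also give 122 and 116.

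**Power with 60 practices per arm.** Power = Φ{0.06 / √[V × (0.1 + 0.9/m) × (1−r²) / 60] − 1.96}, with V = 0.4694 (beta-blockers) or 0.4470 (ACE-inhibitors). For beta-blockers with unlimited m and r = 0: 0.06 / √(0.4694 × 0.1 / 60) = 2.145, and Φ(0.185) = 57%.

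| m | r | Beta-blockers | ACE-inhibitors |
|---|---|---|---|
| 20 | 0 | 43% | 45% |
| 47 | 0 | 50% | 52% |
| 100 | 0 | 54% | 56% |
| unlimited | 0 | 57% | 59% |
| 47 | 0.3 | 54% | 56% |
| 47 | 0.5 | 62% | 64% |
| 47 | 0.7 | 79% | 80% |

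**Detectable difference at 80% power, 60 per arm, r = 0.** Solve d = 2.8016 × √{[p1(1−p1) + (p1+d)(1−p1−d)] × (0.1 + 0.9/m) / 60}. With unlimited m, d is 7.8 points (beta-blockers) and 7.6 points (ACE-inhibitors). At m = 47 it is 8.5 and 8.3 points. The plan assumes 6.

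**The case against.** A reader might infer that the authors computed 122 and 116 per arm and then used them as totals. The fit at one cluster size makes this plausible but does not prove it. The two individual sample sizes stand in the ratio 1,023.4 / 974.6 = 1.050, and 122 / 116 = 1.052, so any calculation that applies one common multiplier and matches the first figure will nearly match the second. The baseline-credit calculations reach the same pair as totals, and the article cannot separate the two explanations. That stands, so the per-arm origin remains an inference.

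A reader might also infer that the trial simply has 50% power. The documents do not support that as a fixed figure either. The cluster size is unknown, and the planned analysis adjusts for the baseline year, so the unadjusted figure is not the power of the analysis to be run. That stands too, and is why the power must be stated conditionally.

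Finally, a condensed article may leave cluster size and correlation to the full protocol. Their absence is not the finding. The finding is that a printed result does not follow from the printed inputs at any cluster size. The adjustment might restore about 80%, but with 122 practices and m = 47 that needs r of about 0.71 for beta-blockers (about 0.64 even with unlimited m), and the Sample size section claims no such gain.

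**Conclusion.** The point holds in conditional form. Under an unadjusted two-arm comparison with the stated proportions and ICC, 122 and 116 cannot be trial totals with 80% power; the minimum totals are about 206 and 196. This conclusion does not depend on the missing cluster size, the choice of formula or the sidedness of the test. For 120 practices without baseline credit, power is at most about 57% and 59%, and about 50% and 52% if m is 47 to 50. With adjustment it could be materially higher, up to about 79% and 80% at r = 0.7 and m = 47, but the article gives no value of r. How the printed figures arose cannot be settled from the article.

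A minor separate inconsistency: the abstract's 120 practices fall below the section's own minimum of 122 completing. The effect on power is under one percentage point (51.1% to 50.4% for beta-blockers at m = 50), and 120 may be a rounded figure.

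**What to change.** Restate the Sample size section as follows.

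1. Say whether 122 and 116 are per arm or total, and give the cluster size and any baseline correlation assumed. If they are per arm, the totals are 244 and 232.
2. Replace the 80% claim for about 120 practices with power and detectable difference on those inputs. Without adjustment: at most 57% and 59%, with detectable differences of at least about 7.8 and 7.6 points. With adjustment at m = 47: about 62% and 64% at r = 0.5, and 79% and 80% at r = 0.7.
3. Check the assumed correlation on the baseline-year data.
4. Reconcile the 120 practices in the abstract with the minimum of 122 completing.

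The Trial status section reports recruitment and follow-up closed, so the number of practices cannot be changed. It also reports no data cleaning or analysis at submission, so the correction can be made before results are known. The cost is rewording, one check on baseline data, and probably a less favourable power statement.

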### Randomization

Eligible general practices will be randomly allocated to either the intervention arm or the control arm, stratified by type of EHRS (MicroHIS X or Promedico-ASP) (see Figure 1). Practices will be the unit of randomization. Before randomization, the practices will be clustered at the level of practice addresses (practice AGB code and zip code) to avoid GPs and practices that are located within the same building being designated to different study groups. Randomization will be central and computer-generated, executed by an independent person (one of the members of the research team without any COI towards allocation). Dedicated software will be used to generate a randomization scheme with an equal number of control and intervention practices.

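### Practices sharing an address are allocated together, but the model's highest level is the practice; if such practices stay correlated after baseline adjustment, the arm effect's standard error is too small

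*Protocol article*

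**What the plan says.** The Randomization section states "Practices will be the unit of randomization". It then adds a step: "Before randomization, the practices will be clustered at the level of practice addresses (practice AGB code and zip code"). The reason given is "to avoid GPs and practices that are located within the same building being designated to different study groups". The same section asks for equal numbers of practices in the two arms.

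The Analysis section says that follow-up scores "will be compared between both study arms adjusted for baseline findings", and that "To take into account potential clustering of effects within practices, multilevel models will be used". It then names the levels: "Both patient-level and practice-level intercept estimates will be used to account for potential correlation of measurements within patients and within general practices". It explains why the provider level is left out. It does not mention an address level.

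The Sample size section also counts practices: "we will need at least 122 general practices completing the trial with 80% power". It uses one intra-cluster correlation of 0.1 and does not name the level to which it applies.

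**The concern.** In a cluster trial the variance of the arm effect has to reflect the units that were allocated independently. Two practices that must go to the same arm are not allocated independently. If their results are also alike, each adds less information about the arm effect than a separately allocated practice would. A model whose highest level is the practice counts them as two independent units. Its standard error is then too small and its test rejects too often under the null.

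At stake are the three prescribing outcomes, and any other between-arm comparison made with the same random-effects structure.

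**Working it through.** **Which unit is allocated, and which is modelled**

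- Allocated (Randomization): the address group, which is a single practice where the address is not shared.
- Modelled (Analysis): patient and practice.
- Counted (Sample size): practices.

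The three agree only if no participating practices share an address, or if a shared address is treated throughout as one practice.

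**The plan's own figure**

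The planned changes are "ACE-inhibitor change from 63%–69%; beta-blockers from 59%–65"%. The pooled two-proportion formula (two-sided 5%, 80% power) is

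n per arm = [1.96·√(2p̄q̄) + 0.84·√(p₁q₁ + p₂q₂)]² / (p₂ − p₁)²

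It gives 1,027 patients per arm for beta-blockers and 978 for ACE-inhibitors before clustering. The design effect is 1 + (m − 1)·0.1, but the cluster size m is not stated.

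- Read as a number per arm, m = 48 gives 1,027 × 5.7/48 = 122.0 and 978 × 5.7/48 = 116.1, which match the stated 122 and 116.
- Read as a total, the unadjusted number cannot fall below 2 × 1,027 × 0.1 = 205.4. A total of 122 then needs an unstated gain from baseline adjustment (a correlation of about 0.71 to 0.83 for m from 50 down to 10).

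So 122 can be neither confirmed nor called wrong. The present point does not depend on it.

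**Effect of the omitted level**

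Assumed inputs, none of which is in the article:

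- f, the share of practices at shared addresses;
- k, the number of practices per shared address;
- r, the correlation between practice means at one address, after baseline adjustment.

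With whole address groups allocated, the variance of the arm contrast relative to the practice-level model, and the actual error rate, are

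V = 1 + f·(k − 1)·r

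Actual two-sided type I error = 2·[1 − Φ(1.96/√V)]

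For pairs (k = 2) and r = 0.5:

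| f | V | Standard error too small by | Actual type I error | Practices for 80% power if 122 was right | Power at 122 |
|---|---|---|---|---|---|
| 10% | 1.05 | 2% | 5.6% | 129 | 78% |
| 20% | 1.10 | 5% | 6.2% | 135 | 76% |
| 30% | 1.15 | 7% | 6.8% | 141 | 74% |

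The fifth column is 122 × V rounded up. The last two columns assume that 122 gives exactly 80% power when the address level is ignored.

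At the low end, 10% in pairs with r from 0.1 to 0.8 gives 5.1% to 5.9%. With f = 0 or r = 0, V = 1 and nothing changes.

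**Check by simulation**

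The set-up was 122 practices, 25 patients each, intra-cluster correlation 0.1, 8,000 runs, with address groups allocated whole. The Monte Carlo standard error is √(0.05 × 0.95/8,000) = 0.24 percentage points.

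| Shared addresses | Type I error, analysed by practice |
|---|---|
| None | 5.3% |
| 20% in pairs, r = 0.5 | 6.0% |
| 30% in pairs, r = 0.5 | 5.8% |
| 50% in pairs, r = 0.5 | 6.9% |

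Analysed by address group, the rate stayed between 4.8% and 5.3%.

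The direction is confirmed. The simulated values lie somewhat below the formula (5.8% against 6.8% at 30% in pairs). Part of the gap may come from how r is defined. With m = 25, a correlation of 0.5 between underlying practice effects is only 0.5 × 0.1/(0.1 + 0.9/25) = 0.37 between observed means. Then V = 1.11 and the error rate is 6.3% at 30% in pairs. The closed-form figures are best read as approximate.

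**The case against.** **The address group may be what the article calls a practice.** The grouping comes before allocation, and equal numbers of practices per arm follow most easily if each group is then treated as one practice. On that reading counting, allocation and modelling agree and the problem disappears. The text allows this reading but does not state it. The Randomization section speaks of several practices in one building, distinct from their address, and the Dutch Hospital Data section links outcomes by practice code. If this reading is intended, a sentence should say so.

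**The article is condensed.** An extra level could sit in a fuller plan. But the Analysis section lists the levels and argues for leaving one out, so the structure is stated and lacks the level of allocation.

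**The effect may be tiny.** This stands in large part. About 120 practices are sought from about 1,100 invited, each with its own registration form. A pair counts only if both practices use one of the two eligible record systems and both enrol. Baseline adjustment also removes part of any stable likeness between neighbours.

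**Stronger readings that the article does not support:**

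- A reader might infer error rates near 10%. With half of all practices in pairs and r = 0.8, V = 1.40 and the rate is 9.8%. Nothing in the article supports such inputs. Even there the variance is understated by 1 − 1/1.40 = 29%, not 40%.
- A reader might assume that co-located practices share staff, patients or working protocols. The article says only that they are in the same building.
- A reader might extend the point to every outcome. Some system-use measures exist in the intervention arm only, and exposure to NHGDoc is analysed descriptively. These involve no test between arms.

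**Conclusion.** The mismatch is in the text: allocation is by address group where addresses are shared, and the model stops at the practice. The consequence is conditional. The standard error is too small only if co-located practices stay positively correlated after baseline adjustment, and only for outcomes analysed with this model.

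On the assumption of 10–30% of practices in pairs and r = 0.5, the true variance is about 5–15% larger than modelled (understated by 1 − 1/V, about 5–13%), and the type I error is roughly 5.6–6.8%. The simulation suggests slightly less. With few shared addresses or little residual correlation the effect is negligible. The article gives neither the number of shared addresses nor the correlation, so no single figure can be claimed. The change is still worth making because it costs very little.

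**What to change.** - In the Analysis section, make the randomised address group the highest-level random intercept, with practice nested within it where that can be estimated. If too few addresses are shared to separate the two levels, use standard errors clustered by address group instead.
- In the Randomization section, name the address group as the unit of randomisation. Report the number of groups per arm beside the number of practices. If an address group is already analysed as one practice, say so; no change to the model is then needed.

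The address grouping is made before randomisation, so the identifier should already exist. The Trial status section says that no data cleaning or analysis had been done at submission, so the model can be changed without knowledge of results. Recruitment is closed, so the number of practices is fixed. The cost is a sentence or two and slightly wider intervals where addresses are shared.

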**Figure 1 Fig1:**
[figure not shown]
**Study flow diagram.** *Stratification will be based on the type of EHRS.

### Blinding

General practices and the staff working within these practices will be blinded to group allocation. They will not be informed about being allocated to either the intervention group or the control group (see ‘Participants’ section). They are even unaware of participating in an intervention trial with a concurrent control group. However, as the intervention arm will, at the onset of the trial, receive decision support on heart failure (directly available to all intervention practices at one preset moment in time) without the usual communication about the implementation of a new module, these practices may suspect heart failure to be the subject/topic of the trial. Therefore, the extent to which the blinding was really successful will be checked in a survey, which is part of the process evaluation of the trial.

Patients will also be blinded to group allocation as they are not aware and are not likely to become aware of the trial (design). Given the fact that patients are not being exposed to experimental interventions and that all patient data used in our evaluation study are anonymized, we are not obliged to inform patients about the use of these data, nor do we have to offer them an opt-out option. And finally, researchers will also be blinded to the group allocation as the randomization variables will be labeled with the letters A and B (rather than I and C) for the control and intervention group by a third independent researcher.

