#### Intervention arm: regular modules plus additional module on heart failure

General practices allocated to the intervention arm will receive the same decision support modules as the control arm (see ‘Description of NHGDoc and its regular modules (control arm)’ section), extended with the NHGDoc module on heart failure, which will be activated at the onset of the trial (see ‘Basic elements/key recommendations of the NHGDoc module on heart failure (intervention arm)’ section). The reason we chose heart failure to be the subject of the trial was first of all of pragmatic nature; heart failure was one of the few modules that were to be implemented into NHGDoc in the year of the onset of the trial. In addition, we chose heart failure as it is a relatively common condition for which relatively large improvements (in terms of increasing or decreasing mortality and morbidity) are to be expected if healthcare providers adhere to the treatment guidelines, compared to other conditions [27-31].

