#### NHGDoc server

For the largest part of this study, existing data collection methods from the NHGDoc alert service that have been developed by ExpertDoc to generate CDSS alerts for NHGDoc will be used. These are all automated data extractions from electronic patient records available in the EHRS. The NHGDoc alert service only uses anonymized patient data, and data are only streamed and not stored. For this evaluation study, however, it is necessary to save the anonymous data for the follow-up period of a year. Therefore, ExpertDoc, the company that manages the data, will send the NHGDoc data on a monthly basis, secured with a log in code, to IQ healthcare. NHGDoc data include all alerts, and the anonymous patient data that generate the alerts.

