### Process evaluation

Aside from the effect evaluation, a process evaluation will be conducted to gain insight into the barriers and facilitators that affect the system’s uptake and impact [35]. The actual exposure of the PCPs to the intervention as well as their experience with the intervention may have affected the results of the study and will be investigated. Results of the process evaluation will be used to improve (the implementation of) NHGDoc.

Data will be collected among participants in the intervention and control arm in three different ways. First, some variables measuring exposure to the intervention (e.g., not functioning of the server, deliberately turning off the heart failure module or particular areas within this module) will be collected by the NHGDoc server.

Second, three focus groups will be conducted among NHGDoc users (eight to ten GPs and PNs per group) to gain insight into their experiences with CDSSs in general and NHGDoc in particular. In each focus group, barriers and facilitators will be discussed using a topic list. Participants will be recruited by sending a direct email and reminders to all participating practices. If necessary, additional announcements will be placed on relevant websites and through social media (i.e., Facebook, Twitter, and LinkedIn).

And finally, an electronic questionnaire will be sent to all participating practices at the end of the study period to triangulate the findings of the study. Aside from quantitatively assessing the perceived barriers and facilitators to using CDSSs in general and NHGDoc in particular, attention will be paid to the exposure to and experiences with the specific heart failure module. Also, the intended ‘blinding’ in terms of the content of the intervention as well as the group allocation will be checked among participants.

Exposure to and experiences with NHGDoc will be analyzed descriptively. Data from the focus groups will be audiotaped, verbatim transcribed, and independently analyzed by two researchers using content analysis with the software program AtlasTi7.0.

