Although NHGDoc is a multiple-domain covering CDSS, the design of the study does not allow us to differentiate in the effects between the various domains of care. The intervention in our trial consists solely of decision support in the area of heart failure. Nevertheless, our study does provide insight into the extent that decision support on heart failure is effective in a setting in which decision support is provided for several domains of care. Moreover, the process evaluation in our study will also provide insight in terms of the uptake and effectiveness of decision support as part of a multiple domain-covering CDSSs as well as its contributing/factors.

A limitation of our study design is that we do not have a ‘real’ control group, consisting of healthcare providers not using NHGDoc at all. Although the control arm does not receive decision support in the area of heart failure, it does receive decision support with respect to the regular NHGDoc modules that had already been implemented at the onset of the trial. This may suggest a selection bias with only GPs and PNs with a positive attitude towards CDSSs participating in the trial. However, both the control and intervention arm consist of general practices that have NHGDoc at their disposal because it is integrated into their EHRS, rather than that they have deliberately chosen for it. As a consequence, it is unlikely that only highly motivated GPs and PNs using NHGDoc frequently participate in our study. Moreover, if there is any bias in terms of motivation among participating GPs, we expect it to be equally distributed between the intervention and control arm, as a result of the randomization process of the trial.

This study will shed light on the uptake and effectiveness of CDSSs covering multiple disease areas in primary care, which is owned and implemented by a national guideline organization. By also exploring factors contributing to the system’s uptake and effectiveness, insight will be provided in how such systems should be designed and implemented in order to function well in a generic primary care setting. Results will not only be of interest to developers and implementers of CDSSs but also to guideline implementers using CDSSs to improve the uptake of guidelines and ultimately patient outcomes in primary care.

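### Labelling the arms A and B cannot by itself blind anyone who handles NHGDoc alert data linked to those labels, because heart failure module alerts occur in the intervention arm only.

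*Protocol article*

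**What the plan says.** The Blinding section makes an unqualified claim for the research team: "researchers will also be blinded to the group allocation as the randomization variables will be labeled with the letters A and B". An independent third researcher applies the letters. No other step to blind researchers is described.

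Other sections describe what separates the arms and what data are delivered:

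- Intervention arm: these practices have the regular modules, "extended with the NHGDoc module on heart failure, which will be activated at the onset of the trial".
- Discussion: "the control arm does not receive decision support in the area of heart failure".
- NHGDoc server (Data collection): the company that manages the system "will send the NHGDoc data on a monthly basis, secured with a log in code, to IQ healthcare". On content, "NHGDoc data include all alerts, and the anonymous patient data that generate the alerts".
- Secondary outcome measures: use of the system includes the "number of practices with at least one user who switched the module heart failure off (intervention group only").
- Process evaluation: the server also records exposure variables such as "deliberately turning off the heart failure module or particular areas within this module".

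The article concedes that participants' blinding may fail and plans a survey to check it. It states no such caveat or check for researchers.

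**The concern.** A letter code masks an arm only if nothing else in the data reveals it. Here the intervention is itself a stream of alerts, and the alerts are part of the study data. The mask covers the allocation variable and leaves the fields that mirror it in view.

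What is at stake is the protection that readers will credit to analyst blinding. The primary outcomes are percentages of consultations in patients with heart failure, built from data transmitted when a patient file is opened. Someone has to settle which openings count as consultations, which patients count as having heart failure, and how practices with the module switched off are treated. Under Trial status the article says that no cleaning or analysis had been done at submission. Any of these choices not already fixed elsewhere could therefore still be made by people able to tell which arm is which.

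**Working it through.** No arithmetic applies, and the plan gives no figure to reproduce. The check is whether the letter code can be broken from data that the article says are delivered or analysed.

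1. **What is confined to one arm.** The sections on the intervention arm and the Discussion agree that heart failure decision support exists only in intervention practices. An alert generated by that module, or a record of that module being switched off, can therefore come only from an intervention practice.

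2. **What is not confined to one arm.** The regular modules, such as cardiovascular risk management and atrial fibrillation, run in both arms and can fire for patients who have heart failure. The secondary outcome "number of requests sent and alerts received for heart failure patients" is thus not arm-specific as a total. The module may raise that total in one arm, but only the module of origin identifies the arm with certainty. Switch-offs of other modules likewise occur in both arms.

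3. **What is delivered.** The data-collection section says all alerts are included, together with the patient data that trigger them. It excludes no module and describes no masking of alert fields. It does not name switch-off records as part of the monthly files. These are collected by the server according to Process evaluation and are needed for a secondary outcome, but the argument does not depend on them, because the alerts are enough.

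4. **What one record reveals.** Suppose a single heart failure module alert belongs to a practice labelled A. By step 1 that practice is in the intervention arm, so A is the intervention and B the control. With two letters for two arms, this settles the allocation of every practice, including intervention practices with no heart failure alert of their own.

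5. **What the analysis itself needs.** The switch-off measure restricted to the intervention group cannot be reported without knowing which letter is the intervention. This need not harm the primary comparison if it comes afterwards, but the article states no order.

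6. **Where bias could and could not enter.** The NHGDoc data are automated extractions from the electronic record. Hospital admissions and mortality come from a separate foundation, selected by practice code and ICD-10 code I50. No researcher judges an outcome at collection. What remains is discretion in cleaning, definitions and modelling.

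**The case against.** The strongest reply is that the article does not say who opens which file. The data go to an institution, and its recipients are not stated to be the blinded researchers. Some separation of roles is described: one person executes the randomization and an independent researcher assigns the letters. Further separation, and the order in which files are opened, could be set out in a full protocol, data management plan or SAP that is not shown. Definitions could be fixed there too. The primary outcomes and the class of model are already stated.

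Much of this stands. A reader might infer that the research team was in fact unblinded, or that the code would be broken on first sight of the monthly files. The documents do not support either. They do not say that the recipients are the blinded researchers, or that the files carry the letters and a visible module identifier. Nor do they say that switch-off records travel in the monthly files.

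The reply does not rescue the claim as worded. The point does not rest on missing detail. The article asserts that researchers are blinded, gives relabelling as the reason, and describes data in which relabelling alone cannot achieve this for anyone who sees both. No section of the article resolves the conflict.

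**Conclusion.** The point holds for anyone who handles NHGDoc alert data linked to the A/B labels. For such a person the stated mechanism gives no blinding, and the loss is complete: one heart failure module record decodes both arms.

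This rests on two assumptions. The first is that the module of origin can be recognised from an alert's content or an identifier, which is plausible given how specific the listed heart failure alerts are. The second is that at least some people covered by the blinding claim work with the alert data. That is the natural reading where no separation is described, but it is not stated.

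A reader might go further and infer that the trial's results will be biased. The article gives no basis for that. Outcome extraction is automated, the exposure is limited to analytic discretion, and neither the direction nor the size of any effect can be derived. The finding is that a safeguard is claimed which the described data flow does not deliver. It is worth correcting because the remedy is cheap, but it does not invalidate the design.

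**What to change.** Have the independent researcher who assigns the letters prepare two files.

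- **Primary-outcome file:** the prescribing data with the A/B label, with all alert, alert-opening and module-status fields removed. It goes to an analyst who has not viewed the alert data. Definitions, cleaning and the A-versus-B analysis of the primary outcomes are completed and locked on this file.
- **Alert and usage file:** alerts, alert openings and module switch-offs, released only after that lock.

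The Blinding section should then say who is blinded and until when.

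The cost is one data-handling step and a sentence of text, and the usage results become available slightly later. Timing limits this option. Follow-up had closed by submission and files were to be sent monthly, so alert data may already have been delivered. The statement that no cleaning or analysis had been done does not rule out that someone had looked at them. The split still works if an analyst who has not viewed them is available. If the analysts have already viewed the alert files, qualify or delete the claim that researchers are blinded, which costs one sentence.
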